### Baseline assessment

Baseline visit and assessment will be conducted at the inpatient centers in the hospitals. Demographic information (including sex, age, educational background, job), course of the chronic pain, medical history (including complications, smoking, alcohol), and basic tests (including blood pressure, heart rate), will be collected in person. Baseline assessment about the chronic musculoskeletal pain will include severity of the pain (assessed by Numerical Rating Scale, range 0–10, higher scores indicate worse pain), pain-related overall life assessment (measured by Global Pain Scale, range 0–200, higher scores indicate worse influence on life), acceptance of pain (assessed by Chronic Pain Acceptance Questionnaire, range 0–120, higher scores indicate higher pain acceptance), health education and self-management (assessed by the Health Education Impact Questionnaire, range 40–200, higher scores indicate better health self-management), pain-related self-efficacy (assessed by the Pain Self-Efficacy Questionnaire, range 0–60, higher scores indicate better confidence of self-efficacy), anxiety and depression (assessed by the Hospital Anxiety and Depression Scale, range 0–42, higher scores indicate more severe symptoms), and quality of life (assessed by Short Form-36, range 0–100, higher scores indicate better health). All scheduled visits are shown in the Table 1.

**Table 1 tab1:** The schedule of planned visits.

Study component	Visit 1	Visit 2	Visit 3	Visit 4	Visit 5	Visit 6	Visit 7	Visit 8
Time	1 d before treatment	First treatment	7 ± 1 d after treatment	14 ± 1 d after treatment	21 ± 1 d after treatment	28 ± 1 d after treatment	35 ± 1 d after treatment	42 ± 1 d after treatment
Informed consent	×	–	–	–	–	–	–	–
Demographic	×	–	–	–	–	–	–	–
Pain duration	×	–	–	–	–	–	–	–
Pain locations	×	–	–	–	–	–	–	–
Pain triggers	×	–	–	–	–	–	–	–
Randomization	×	–	–	–	–	–	–	–
Intervention	–	×	×	×	–	–	–	–
NRS	×	–	×	×	–	–	–	×
GPS	×	–	×	×	–	–	–	×
CPAQ	×	–	×	×	–	–	–	×
heiQ	×	–	×	×	–	–	–	×
PSEQ	×	–	×	×	–	–	–	×
HADS	×	–	×	×	–	–	–	×
SF-36	×	–	×	×	–	–	–	×
Pain killer intake	×	–	×	×	–	–	–	×
Adverse events	–	×	×	×	×	×	×	×

NRS, Numerical rating scale; GPS, Global pain scale; CPAQ, Chronic pain acceptance questionnaire; heiQ, Health Education Impact Questionnaire; PSEQ, Pain Self-Efficacy Questionnaire; HADS, Hospital anxiety and depression scale; SF-36, Short Form-36.

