### Follow-up visit

The visits will be conducted at the day when patients receive the first treatment, and 7 days, and 14 days after the first treatment, which will be during the intervention duration of 2 weeks. After the end of the intervention, the follow-up visits will be done at day 21, day 28, day 35, and day 42 after the first treatment, which is 1 month follow-up after the intervention.

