### Study outcomes and assessment

The primary outcome is the change in the score of Global Pain Scale (GPS, range 0–200, higher scores indicate worse influence on life) from baseline to the end of the 2 week intervention. The GPS is a validated, concise, and easily interpreted score to comprehensively assess the pain, emotions, clinical outcomes, and daily activities (11). The Chinese version of the GPS was also validated in Chinese population (12).

The secondary outcomes include (1) the change in GPS from baseline to the end of 6 week follow-up; (2) the proportion of participants who have clinically significant change in severity of the pain assessed by Numerical Rating Scale (NRS, range 0–10, higher scores indicate worse pain) (13), a change of 20% from baseline to the end of the 2 week intervention is regarded as clinically significant change (14); (3) the change in acceptance of pain assessed by Chronic Pain Acceptance Questionnaire(CPAQ, range 0–120, higher scores indicate higher pain acceptance) from baseline to the end of 2 week intervention (15); (4) the change in health education and self-management assessed by the Health Education Impact Questionnaire (heiQ, range 40–200, higher scores indicate better health self-management) from baseline to the end of 2 week intervention (16); (5) the change in pain-related self-efficacy assessed by the Pain Self-Efficacy Questionnaire (PSEQ, range 0–60, higher scores indicate better confidence of self-efficacy) from baseline to the end of 2 week intervention (17); (6) the change of anxiety and depression assessed by the Hospital Anxiety and Depression Scale (HADS, range 0–42, higher scores indicate more severe symptoms) from baseline to the end of 2 week intervention (18); (7) the change in quality of life assessed by Short Form-36 (SF-36, range 0–100, higher scores indicate better health) from baseline to the end of the 2 week intervention (19).

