### Statistical analysis

The Primary analysis will be conducted on the full dataset of all the participants after randomization based on the intention-to-treat principle. Moreover, sensitivity analysis will be conducted between the full dataset and the per protocol dataset. Participants who are not in the per protocol analysis are nonadherence which might be caused by failure to receive the assigned treatment, suffering from severe adverse events, or loss of follow-up.

To check if there is selection bias and confounding factors, we will compare the baseline characteristics of the two groups. Continuous variables will be described as mean (Standard Deviation) for normal distribution and be tested using t test or be described as median (interquartile range) for skewed distribution and be tested using Mann–Whitney test. Categorical variables will be summarized as counts (percentages) and be tested using Chi squared test or Fisher exact test.

The primary outcome of this trial is the change in Global Pain Scale from baseline to the end of the 2 week intervention. The difference of the changes between the two groups will be analyzed using a generalized linear mixed model. The mean and 95% confidence interval will be calculated and estimated. Known confounding factors that may affect the pain severity in chronic musculoskeletal patients include age, sex, job, duration of the chronic pain, and emotional state. Therefore, we will make the subgroup analysis for the variables of age categories (>60 years vs. ≤60 years), sex (female vs. male), job categories, duration of pain, taking these as covariates in the model.

For the secondary outcomes, generalized linear mixed model will be used for continuous variables, and two proportion z test will be used for proportions, whereas the Chi squared test or Fisher exact test will be used for categorical variables.

The primary economic analysis will be the cost-utility analysis over 6 week using quality-adjusted life years (QALYs) calculated from the SF-36. The mixed-effect linear regression model will be used, adjusting the confounding factors including age, sex, job, and site of recruitment.

All statistical tests will use the statistical significance of 2-sided *p* value of <0.05. All the statistical analysis will be performed using Python, version 3.8.16 (sklearn and statsmodels packages).

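### The QALY regression names age, sex, job and site as covariates but not baseline utility, although the SF-36 is collected at baseline and enters each patient's QALY

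*Protocol article*

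**What the plan says.** In the protocol article, the Statistical analysis section commits to an economic evaluation: "The primary economic analysis will be the cost-utility analysis over 6 week using quality-adjusted life years (QALYs) calculated from the SF-36". The next sentence gives the model: "The mixed-effect linear regression model will be used, adjusting the confounding factors including age, sex, job, and site of recruitment".

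The Baseline assessment section includes "quality of life (assessed by Short Form-36, range 0–100, higher scores indicate better health" among the baseline measures. Table 1 in the same section marks the SF-36 at Visits 1, 3, 4 and 8, which are baseline and days 7, 14 and 42. The Follow-up visit section confirms the horizon: "follow-up visits will be done at day 21, day 28, day 35, and day 42 after the first treatment".

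Among the outcomes, the SF-36 appears only as "the change in quality of life assessed by Short Form-36" from baseline to the end of the two-week intervention. No cost or QALY outcome is listed. On the resource side, the one relevant row of Table 1 is "Pain killer intake", at Visits 1, 3, 4 and 8.

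**The concern.** A QALY over six weeks is an area under a utility curve that starts at baseline. If the arms differ at baseline by chance, the QALY difference moves in two ways: directly, because the baseline value is part of the area, and indirectly, because patients who start higher tend to stay higher. Age, sex, job and site will generally not remove this; the baseline value of the same measure does.

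A six-week horizon leaves room only for a very small QALY difference. A modest chance imbalance can therefore be as large as the effect sought, and it would pass into any incremental cost-effectiveness ratio.

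**Working it through.** The article gives no figure for the economic analysis, so there is none to reproduce. Its sample size for the primary outcome does reproduce: a difference of 4 with SD 6.7, 80% power and two-sided 0.05 gives 45.02 by the t-test, rounded up to 46 per group, and 92 / 0.8 = 115. It does not bear on this point.

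**Inputs from the article.** SF-36 at days 0, 7, 14 and 42; 46 per group required and 120 planned, which is 60 per arm.

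**Assumptions, not in the article.** Utility SD 0.08 to 0.20, equal over time; correlation r between baseline and each later value 0.5 to 0.7; utility gain 0.02 to 0.05.

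**Step 1, weights.** The trapezoid rule gives the four time points 3.5, 7, 17.5 and 14 days, which sum to 42. As shares these are 8.3%, 16.7%, 41.7% and 33.3%. In years (divided by 365.25) they are 0.00958, 0.01916, 0.04791 and 0.03833, which sum to 0.1150.

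**Step 2, carry-over.** A baseline difference D shifts the expected unadjusted QALY difference by D × [0.00958 + r × (0.01916 + 0.04791 + 0.03833)].
- r = 0.5: D × 0.0623
- r = 0.7: D × 0.0834

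The direct baseline part is the smaller one: 0.00958 / 0.0623 = 15% and 0.00958 / 0.0834 = 11% of the shift. The rest comes through correlation.

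**Step 3, one standard error of chance imbalance.** D = SD × √(2/n).

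| SD | n per arm | D | Shift, r = 0.5 | Shift, r = 0.7 |
|---|---|---|---|---|
| 0.08 | 60 | 0.0146 | 0.0009 | 0.0012 |
| 0.08 | 46 | 0.0167 | 0.0010 | 0.0014 |
| 0.12 | 60 | 0.0219 | 0.0014 | 0.0018 |
| 0.12 | 46 | 0.0250 | 0.0016 | 0.0021 |
| 0.20 | 60 | 0.0365 | 0.0023 | 0.0030 |
| 0.20 | 46 | 0.0417 | 0.0026 | 0.0035 |

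**Step 4, an effect for comparison.** A gain g, half reached at day 7, full at day 14 and held to day 42, is worth g × (0.5 × 0.01916 + 0.04791 + 0.03833) = g × 0.0958.
- g = 0.02: 0.0019 QALY
- g = 0.05: 0.0048 QALY

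**Secondary check, cost side.** The Interventions and control section plans 3 × 2 = 6 massage sessions, or plasters twice a day for two weeks. Planned quantities need not equal delivered ones: the sample size section allows 20% dropout, and the analysis section expects nonadherence. Plaster use also depends on the number of painful sites, and the inclusion criteria admit fibromyalgia with pain in at least 4 of 5 body regions. If one plaster is used per site per application (an assumption), one site needs 2 × 14 = 28 and four sites need 112.

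**The case against.** Three points can fairly be made for the plan.

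- The covariate list reads "adjusting the confounding factors including age, sex, job, and site of recruitment", and its wording leaves room for others. That stands, but room for a covariate does not commit the analysis to it, and this is the covariate most closely tied to the QALY.
- Randomization makes the unadjusted difference unbiased in expectation. That stands in full: the loss is precision, plus the chance imbalance that happens to occur in this trial.
- The model sentence does not name the dependent variable. A mixed model that takes the repeated utilities as outcomes, with a common baseline mean in both arms, would also deal with baseline. The article does not describe such a model.

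A reader might go further and infer that the cost-utility analysis cannot be done because no costs or resource use are collected. The article does not support that. Pain killer intake is scheduled four times and the planned treatment quantities are fixed, so a narrow costing with external prices is possible. Table 1 is also not a complete list: blood pressure, smoking and the expectation score mentioned in the Discussion have no row. The case report forms and full protocol are not shown, and cost items, perspective and the conversion from SF-36 to utility are details that an article may leave to them. Nor does the article say that the 0–100 score itself will serve as a utility.

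A reader might also take a baseline imbalance of 0.05 persisting in full as the size of the problem: 0.05 × 6/52 = 0.0058 QALY. That overstates it. The 0.05 exceeds one standard error in every scenario above, and with r of 0.5 to 0.7 it would shift the result by 0.0031 to 0.0042.

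**Conclusion.** The point holds in a limited form. The QALY model does not name baseline utility, although baseline SF-36 is scheduled for every patient. Under the assumptions stated, a one-standard-error imbalance shifts the unadjusted QALY difference by 0.0009 to 0.0035, against an assumed effect of 0.0019 to 0.0048. A valid unadjusted confidence interval already allows for such imbalance on average, so the cost is a wider interval and an estimate that is easily moved by chance. The SDs, correlations and gains are assumptions; other values would change the sizes but not the direction.

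On costs, only a question for the sponsor remains: whether use beyond pain killers is recorded in the unseen forms. The economic analysis is neither a primary nor a secondary outcome, and nothing here touches the efficacy conclusion or the sample size.

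**What to change.** Add the baseline SF-36-derived utility as a covariate in the QALY model, and state that QALYs are the area under the curve over baseline and days 7, 14 and 42. This needs one sentence and no new data.

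Separately, the sponsor should confirm that sessions delivered, plasters used and other care are recorded in the case report forms. If they are not, either limit the claim to an intervention-plus-analgesic costing or withdraw the cost-utility analysis. Limiting or withdrawing it costs only a change of text. Starting to record these items would take about one form page, and for patients already enrolled sessions and plasters would have to come from treatment records. The article gives November 2022 as the start of recruitment and September 2024 as the expected end, and resource use not recorded during follow-up is hard to recover, so the check should be made early.

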## Discussion

This is the first randomized clinical trial to investigate the heat-stone massage as a kind of therapy alone to treat chronic musculoskeletal pain. Currently, no massage therapy has been recommended by any of the chronic musculoskeletal pain management guideline due to lack of evidence. Finding a therapy which is easy to use and has long-term effect with low cost for the management of chronic musculoskeletal pain will change the clinical practice of this chronic pain and will change the life quality of the patients. Our pilot study showed a promising result in terms of long-term symptoms relief, but we need strong evidence to prove this. The results of this multicenter, randomized, clinical trial will provide high-quality evidence, which is promising to change the guideline for chronic pain management in the future.

The strengths of this study include: (1) randomization can reduce the selection bias and control both measured and unmeasured confounding factors; (2) inclusion criteria of chronic musculoskeletal pain and standard procedure of the heat-stone massage increase the external validity and application of the intervention; (3) prespecified subgroup analysis can identify any interaction on the causal pathway between the heat-stone massage and pain relief outcome, which will effect modifiers that are crucial when we interpret the results.

This trial also has limitations. First, this trial is only blinded to principal investigator, outcome assessment staff, and outcome analysis statistician, but not blinded to participants or massage therapists, therefore there might be performance bias. Nevertheless, we design the expectation score to evaluate if the expectation is different between groups after they know what we are receiving. Second, although the trial has follow-up visits of 1-month, longer term effect cannot be known, which somehow limits the interpretation of long-term effect of pain relief. Third, we only recruit patients with the moderate pain assessed by NRS score in the range of 4–6, based on the results of our pilot study showing that patient with NRS score between 4 and 6 benefited from the heat-stone massage. This will restrict the chronic pain population that the results of this study can be generalized to, and patients with more severe pain may not benefit.

This multicenter, randomized, controlled, clinical trial will test the hypothesis that heat-stone massage can improve the pain of adult patients with chronic musculoskeletal pain. The results will provide the evidence of the efficacy and safety of heat-stone massage, which might lead to the update of clinical guidelines and change the routine practice.

## Ethics statement

The Ethics Committee of Guang'anmen Hospital approved the study protocol; the most recent version of the protocol (version 2.0) was approved on 25 January 2022. All participants will sign the informed consent form before formal enrollment in our study.

